## Abstract

**Background:**

Sepsis-induced cardiomyopathy significantly increased the mortality of patients with sepsis. The diagnostic criteria for septic cardiomyopathy has not been unified, which brings serious difficulties to clinical treatment. This study aimed to provide evidence for the early identification and intervention in patients with sepsis by clarifying the relationship between the ultrasound phenotype of septic cardiomyopathy and the prognosis of patients with sepsis.

**Methods:**

This was a multicenter, prospective cohort study. The study population will consist of all eligible consecutive patients with sepsis or septic shock who meet the Sepsis 3.0 diagnostic criteria and were aged ≥18 years. Clinical data and echocardiographic measurements will be recorded within 2 h, at the 24th hour, at the 72nd hour, and on the 7th day after admission. The prevalence of each phenotype will be described as well, and their association with prognosis will be analyzed statistically.

**Discussion:**

To achieve early recognition, prevent reinjury, achieve precise treatment, and reduce mortality in patients with sepsis, it is important to identify septic cardiac alterations and classify the phenotypes at all stages of sepsis. First, there is a lack of studies on the prevalence of each phenotype in Chinese populations. Second, each phenotype and its corresponding prognosis are not clear. In addition, the prognosis of patients with normal cardiac ultrasound phenotypes vs. those with suppressed or hyperdynamic cardiac phenotypes is unclear. Finally, this study was designed to collect data at four specific timing, then the timing of occurrence, duration, changes over time, impact to outcomes of each phenotype will probably be found. This study is expected to establish a standard and objective method to assess the ultrasound phenotype of septic cardiomyopathy due to its advantages of visualization, non-invasiveness and reproducibility, and to provide more precise information for the hemodynamic management of septic patients. In addition, this research will promote the clinical application of critical care ultrasound, which will play an important role in medical education and make ultrasound the best method to assess cardiac changes in sepsis.

**Trial registration:**

https://clinicaltrials.gov/ct2/show/NCT05161104, identifier NCT05161104.

## Introduction

Sepsis is a life-threatening organ dysfunction resulting from a dysregulated host response to infection (1). The heart is one of the most important organs for oxygen supply and consumption and is frequently involved in sepsis. Septic myocardial suppression increases mortality in patients (2). Recent studies have found that a hyperdynamic state of the left ventricle (left ventricular ejection fraction [LVEF] >70%) is associated with mortality in intensive care unit (ICU) patients with sepsis, possibly because it reflects unresolved vascular paralysis from sepsis (2). For septic myocardial suppression, there is still a lack of uniform criteria for diagnosis; however, it is well established that the cardiac ultrasound phenotype of septic myocardial suppression can be left ventricular systolic dysfunction (LVSD), left ventricular diastolic dysfunction (LVDD), right ventricular dysfunction (RVD), diffuse ventricular dysfunction, and mixed ventricular dysfunction. According to available literature statistics, the prevalence of LVSD ranges from 12 to 60%, the prevalence of LVDD is higher at 20% to 79%, and the prevalence of RVD varies from 30 to 55% (3). However, based on the current understanding of septic myocardial suppression, the relationship between each stage and its prognosis is unclear. Echocardiography can rapidly identify septic myocardial suppression and guide its classification, thus further optimizing the diagnosis and treatment process of sepsis, particularly to avoid over-resuscitation during fluid resuscitation and perform reverse resuscitation in a timely manner to improve patient prognosis and reduce hospitalization time. This study aimed to classify and evaluate the prognosis of patients with different septic cardiac ultrasound phenotypes in multiple centers across China by measuring the right and left heart systolic and diastolic indices through echocardiography, recording the baseline conditions and clinical indices of patients, and combining them with their prognosis. Thus, in this study, a standardized evaluation system was established to evaluate the cardiac ultrasound phenotype of sepsis patients for the early identification of septic cardiac changes and classification of cardiac phenotypes in various stages of sepsis and to further alleviate sepsis treatment problems caused by the disease. This study also demonstrates the benefits of ultrasound in clinical dynamics and individualized assessment, with medical students gaining not only a convenient tool in their education, but also the clinical thinking skills needed to match it.

## Methods

### Inclusion criteria

The present study will be conducted in several medical centers in China, including Fujian Provincial Hospital, West China Hospital of Sichuan University, Peking Union Medical College Hospital, Fourth Hospital of Hebei Medical University, Chinese PLA General Hospital, First Peopl*e*'s Hospital of Hangzhou City Affiliated to Zhejiang University, First Affiliated Hospital of Xiamen University, Shandong Provincial Hospital Affiliated to Shandong First Medical University, the Affiliated Hospital of Qingdao University, Quanzhou First Hospital affiliated to Fujian Medical University, the First Affiliated Hospital of Anhui Medical University, between April 2022 to April 2025. Informed consent will be obtained from all patients or their legal guardians. All patients with sepsis or septic shock who diagnosed using the Sepsis 3.0 diagnostic criteria (1) and were ≥18 years of age who admitted or hospitalized to each center will be included. Sepsis is defined as an increasing of ≥2 points from baseline in the Sequential Organ Failure Assessment (SOFA) score due to infection, and septic shock is defined as persistent hypotension on top of sepsis, requiring vasoactive drugs to maintain a mean arterial pressure ≥65 mmHg and a blood lactate level >2 mmol/L despite adequate fluid resuscitation. Patients will be admitted to the ICU, and transthoracic echocardiograms will be performed by relevant qualified personnel and interpreted by two qualified personnel. Two senior sonographers (A and B) will independently examine the patients and compare them to identify the true positives as accurately as possible. The agreement rate between the two specialists is as high as 100%, and the reconfirmation of the individual set with doubts reach a unified conclusion. In case of diagnostic disagreement, we will ask an expert panel for a resolution, and as a quality control, all ultrasound images and measurements of each enrolled patient will be recorded. In addition, the results will be compared with the latest guidelines before building the dataset. Patients eligible for inclusion will have their first echocardiogram examination completed within 2 h of admission. If eligible, informed consent will be required prior to formal study entry.

### Exclusion criteria

The exclusion criteria included patients with the following situations:

Preexisting chronic heart disease, such as cardiomyopathy, chronic pulmonary heart disease, severe cardiac valve disease, coronary heart disease, congenital heart disease, and pericardial disease, and with cardiac function of grade ≥III (NYHA classification) prior to sepsisEnd-stage malignanciesSevere traumaPregnancyPatients for whom transthoracic echocardiography data are not available.

### Data acquisition

This study has been approved by the local ethics committee of every participated center. The continuous inpatient electronic medical records will be reviewed for sepsis between April 2022 to April 2025. The prevalence of septic myocardial suppression has been reported in previous literature as 10–70% (4), taking the middle value of 40%. With a 95% confidence level, the results were required to fall within 10% of the overall truth rate, and the required sample size was estimated to be at least 1,152 cases. Detailed demographic and clinical characteristics will be collected and recorded, including age, sex, height, weight, primary diagnosis, site of infection, etiology (if known), underlying disease (hypertension, diabetes, coronary artery disease, chronic kidney disease, chronic obstructive pulmonary disease, oncologic disease, autoimmune disease, etc.), and medication history (beta-blockers, digitalis analogs, hormones, immunosuppressive agents, antineoplastic drugs, etc.).

Clinical and laboratory data will be collected included temperature, heart rate, respiratory rate, peripheral oxygen saturation, blood pressure (systolic/diastolic), pH, partial pressure of oxygen, inspired oxygen concentration, Glasgow Coma Scale score, white blood cell count, neutrophil count, lymphocyte count, hematocrit level, platelet count, calcitonin level, G-test scores, serum albumin level, total bilirubin level, serum creatinine level, troponin I level, NT-proBNP level, maximum dose of vasoactive drugs (norepinephrine, dopamine, vasopressin) or cardiac drugs (dobutamine, levosimendan, desacetyl trichothecene), SOFA score, and APACHE II score.

The ultrasound parameters are as follows:

Indicators of left ventricular systolic function: mitral annular plane systolic excursion (MAPSE), LVEF, and left ventricular outflow tract flow velocity time integralIndicators of left ventricular diastolic function: E, A, and *e*'Right ventricular function indicators: tricuspid annular plane systolic excursion (TAPSE), inferior vena cava end-expiratory and end-inspiratory internal diameters, and right/left heart diastolic basal segment transverse diameter ratio (apical four-chamber heart view)Basal status indicators: right ventricular free wall thickness (subxiphoid four-chamber cardiac section) and septal thickness (apical four-chamber cardiac section).

The hemodynamic parameters will be collected included the central venous pressure, central venous–arterial blood carbon dioxide partial pressure difference, central venous oxygen saturation, and arterial blood lactate concentration.

All parameters mentioned above will be recorded within 2 h after sepsis diagnosis in the ICU, followed by recording of the ultrasound parameters and hemodynamic parameters once at 24, 72 h, and 7 days.

The prevalence of each phenotype will be described firstly. The primary outcomes are in-hospital and 28-day mortality rates. The secondary outcomes are the degree of echocardiographic improvement on day 7, length of stay in the ICU, and number of days on mechanical ventilation. Severe and irreversible disease will be determined by the supervising physician, and the patient's family chose automatic discharge due to local customary conditions indicating death.

If a respondent is absent at a point in time when access is required, resulting in missing data at that point in time, or if an ending visit is missed, data from other points in time can be included in the analysis for that point in time without affecting the integrity and accuracy of the data at other points in time. We will ensure that the data collection was standardized and controllable, with the advantages of complete information, consistent structure, and no redundant information. In the process of data collection, we use the case report form to extract the clinical information required for the study from the research subjects, convert it into a standardized data form, and construct a reasonable database.

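### The stated inputs (40% prevalence, 95% confidence, within 10%) give 93 or 577 patients, not the stated minimum of 1,152

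*Protocol article*

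**What the plan says.** The sample size is set out in the Data acquisition section of the Methods, in two sentences.

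- Expected prevalence: "The prevalence of septic myocardial suppression has been reported in previous literature as 10–70% (4), taking the middle value of 40" per cent.
- Confidence: "With a 95% confidence level".
- Precision: "the results were required to fall within 10% of the overall truth rate".
- Result: "the required sample size was estimated to be at least 1,152 cases".

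The article does not say whether the 10% is absolute or relative. It gives no formula and mentions no design effect, loss allowance, per-group multiplication or power. The abstract describes the design thus: "This was a multicenter, prospective cohort study". Nothing in the sample-size sentences links that design to the number.

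**The concern.** The article prints the inputs and the answer together, as a derivation, so a reader can check one against the other. They disagree by a factor of about 2 on one reading of the 10% and about 12 on the other. This is the only sample-size justification in the article.

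What is at stake is what the number means. If an undisclosed doubling was applied for clustering or loss, the study promises about ±4 points at 40%. If nothing was applied, 1,152 promises about ±2.8 points. If the calculation was really run at 25%, the stated planning prevalence is wrong. A reader judging the eventual prevalence estimate against its planned precision cannot tell which of these applies.

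**Working it through.** **Inputs** (all from Data acquisition)

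- p = 0.40, the midpoint of the quoted range: (10 + 70)/2 = 40%.
- 95% confidence, taken as two-sided, z = 1.96. The article does not state sidedness.
- Margin d: 0.10 if absolute, or 0.10 × 0.40 = 0.04 if relative.
- Stated n: 1,152.

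**Formula:** n = z² p(1 − p)/d², with z² p(1 − p) = 3.8416 × 0.24 = 0.921984.

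**Attempt to reproduce 1,152 from the stated inputs**

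- Absolute, d = 0.10: 0.921984/0.01 = 92.2, so 93. The stated figure is 1,152/93 = 12.4 times this.
- Relative, d = 0.04: 0.921984/0.0016 = 576.24, so 577. The stated figure is 1,152/577 = 2.0 times this.

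**Variants of the same calculation**

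| Variant | Absolute | Relative |
|---|---|---|
| One-sided 95% | 65 | 406 |
| z = 2 | 96 | 600 |
| Continuity correction | 102 | 601 |
| 10% as total width | 369 | 2,305 |

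Inflating 577 for 10%, 20% or 30% loss gives 642, 722 or 825. Dividing 577 by the modelling or validation share of the 7:3 split gives about 824 or 1,923. None of these is 1,152.

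**What does give 1,152**

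- A factor of 2 on the relative result: 2 × 576.24 = 1,152.48. A design effect of 2 would do this, and so would an allowance for 50% loss (576.24/0.5).
- A prevalence of 25% with 10% relative error: 3.8416 × 0.25 × 0.75/0.025² = 0.7203/0.000625 = 1,152.48.

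These two routes give the same number for an algebraic reason. With relative error r, n = (z²/r²) × (1 − p)/p = 384.16 × (1 − p)/p. The ratio (1 − p)/p is 1.5 at 40% and 3 at 25%, exactly double. The number alone therefore cannot show which route was taken.

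**What 1,152 delivers at 40%**

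- Simple random sampling: 1.96 × √(0.24/1,152) = 0.0283, or ±2.8 points; 0.0283/0.40 = 7.1% relative.
- Design effect of 2 (effective n = 576): 1.96 × √(0.24/576) = 0.0400, or ±4.0 points; 10% relative.

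**The case against.** The strongest reply is that 1,152 is twice the relative-error result to within rounding, so a deliberate factor of 2 is a plausible source in a multicentre study. If it was a design effect, the stated 10% relative precision is met. An article condenses a fuller protocol and may have dropped the multiplier. The number is also presented as a minimum and lies above both recomputed values.

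Most of this stands. It rules out any claim that the study is too small for overall prevalence, or that the 10% target is shown to be missed. It does not rescue the derivation. The article offers 1,152 as the consequence of three printed inputs, and it is not. The 25% route fits just as well and conflicts with the printed 40%, so the factor of 2 remains a guess.

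A reader might also infer stronger points that the article does not support.

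- *Precision fails for the rarer phenotypes.* The Introduction reports that "the prevalence of LVSD ranges from 12 to 60%, the prevalence of LVDD is higher at 20% to 79" per cent, and 10% relative precision is harder to reach at the low ends of those ranges. But the 10% target is attached to overall suppression. The article promises only to describe each phenotype's prevalence, with no stated margin.
- *Clustering by centre overwhelms the number.* The article gives no intraclass correlation. Its list of 11 hospitals is introduced as examples and not as the full set, so any figure would rest on assumed values.
- *The study is underpowered for mortality.* It is true that "The primary outcomes are in-hospital and 28-day mortality rates", while the number rests on prevalence. That is a separate matter from this arithmetic. The mortality rates in the Discussion are background literature and not design assumptions.

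**Conclusion.** The point holds as an arithmetic mismatch. At 40% prevalence and two-sided 95% confidence, the stated margin requires 93 patients (absolute) or 577 (relative), against 1,152 stated. Reaching 1,152 takes either an unstated factor of 2 or a prevalence of 25% that contradicts the text. The result rests on the standard normal-approximation formula for one proportion, and none of the usual variants above changes it.

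The error is in the safe direction for overall prevalence. It gives no ground for enlarging the study, and it says nothing about precision by phenotype or power for mortality. What needs correcting is that the only planning figure in the article cannot be reproduced from its own inputs.

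**What to change.** Keep 1,152 and correct the derivation in Data acquisition.

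1. State whether the 10% is absolute or relative, and show the formula.
2. If a multiplier was used, name it and say what it covers, such as a design effect or loss allowance. With a design effect of 2, give the resulting precision as about ±4.0 points at 40%.
3. If the calculation was run at a prevalence other than 40%, say so and reconcile it with the sentence that adopts 40%.
4. If there was no multiplier and 40% stands, replace the 10% target with what 1,152 delivers: about ±2.8 points at 40% (7.1% relative). Say that this assumes simple random sampling.

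The cost is a wording change. No patients, visits or analyses are added.

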### Data statistical analysis

SPSS (version 23.0; SPSS Inc., Chicago, IL, USA) will be used for the analysis. Continuous variables will be defined as the mean ± standard deviation, and categorical variables will be presented as percentages. The Kolmogorov–Smirnov test will be used to verify the normality of the distribution of the continuous variables. One-way ANOVA will be used for comparison of means between groups; two independent samples *t*-test will be used for comparison between two groups; χ^2^ test will be used for counting data; and multifactor logistic regression and Cox survival analysis will be used to determine the factors of prognosis. P-values < 0.05 will be considered statistically significant.

The participants will be divided into a modeling cohort and a validation cohort in a 7:3 ratio. In the modeling cohort, variables with *P* < 0.05 in the univariate Cox analysis will be included in the multivariate Cox analysis, and nomogram plots will be constructed. Finally, the validation cohort will be used to evaluate the discrimination ability of the model based on the area under the ROC curve.

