## Discussion

Several studies have confirmed the high mortality rate in patients with sepsis, ranging from 34 to 56% (5) and 33.5% (6) in foreign and domestic countries, respectively, and even higher in patients with combined hyperdynamic left ventricular function or myocardial depression (3, 7). Standardizing the staging of myocardial depression in sepsis and realizing the early identification of patients with sepsis are of great significance for clarifying the cardiac changes in sepsis at various stages, adjusting and guiding treatment in a timely manner, and optimizing hemodynamics.

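### ICU stay and ventilator days are compared as raw means with no allowance for death, so a deadlier phenotype can appear to need less ICU care when deaths come early

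*Protocol article*

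**What the plan says.** The Data acquisition section of the protocol article names in-hospital and 28-day mortality as primary outcomes. The secondary outcomes are echocardiographic improvement by day 7 and two durations: "length of stay in the ICU, and number of days on mechanical ventilation". Neither duration is defined further. The same paragraph takes discharge at the family's choice, in severe and irreversible disease, to indicate death.

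The Data statistical analysis section gives general rules. For description: "Continuous variables will be defined as the mean ± standard deviation". For more than two groups: "One-way ANOVA will be used for comparison of means between groups". For two groups: "two independent samples *t*-test will be used for comparison between two groups". The regression methods have another purpose: "multifactor logistic regression and Cox survival analysis will be used to determine the factors of prognosis". The threshold is stated as "P-values < 0.05 will be considered statistically significant".

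The Discussion reports sepsis mortality "ranging from 34 to 56% (5) and 33.5% (6) in foreign and domestic countries, respectively", and says that it is higher still with hyperdynamic left ventricular function or myocardial depression.

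The article mentions no ICU-free or ventilator-free days, competing-event analysis, survivors-only analysis or composite ranking.

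**The concern.** A count of ICU or ventilator days stops at death just as it stops at recovery. A patient who dies on day 2 contributes 2 days, and one who recovers and leaves on day 9 contributes 9. On a comparison of means, the death reads as the shorter and apparently better course. Discharge counted as death has the same effect, at a time set by the family's decision.

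This matters here because the groups are cardiac phenotypes that the article itself expects to differ in mortality. Two of the three secondary outcomes could then mix lethality with speed of recovery. A phenotype with early deaths could be reported as needing less ICU care or ventilation, and a longer course among its survivors could be hidden. The problem is separate from skewness, because a rank test on the same raw durations has the same fault.

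**Working it through.** The article gives no figure for this analysis to reproduce, and no durations. All day counts below are assumptions, so a range is shown.

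**Formula.** Let m be mortality in a group, S the mean stay of survivors and D the mean stay of decedents.

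Mean stay = (1 - m) × S + m × D

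If S and D are the same in both phenotypes, the difference (deadlier minus other) is

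(m1 - m2) × (D - S)

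This is negative if D < S, zero if D = S and positive if D > S. The same identity holds for ventilator days.

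**Step 1: mortality at the two ends of the Discussion's figures.** Take m1 = 56% and m2 = 33.5%, a gap of 0.225, and assume S = 10 days.

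| D (days) | Mean at 33.5% | Mean at 56% | Difference |
|---|---|---|---|
| 3 | 7.66 | 6.08 | -1.58 |
| 5 | 8.33 | 7.20 | -1.13 |
| 8 | 9.33 | 8.88 | -0.45 |
| 12 | 10.67 | 11.12 | +0.45 |

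With the same survivors, ICU-free days to day 28 (death = 0) are 0.665 × 18 = 12.0 and 0.44 × 18 = 7.9. The deadlier group is then worse whatever D is. Because survivors are identical here, that gap reflects mortality alone.

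**Step 2: a narrower mortality gap, with the t-test.** Assumed inputs:
- Group sizes are 461 and 691, from the article's 40% prevalence and 1,152 patients (0.40 × 1,152 = 460.8).
- Mortality is 45% vs 28%. The pooled value is (461 × 0.45 + 691 × 0.28) / 1,152 = 34.8%, near the cited 33.5%.
- Survivor stay is lognormal with median 9 days and log-SD 0.7, so S = 9 × exp(0.7²/2) = 11.5 days in both groups.

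The difference is 0.17 × (D - 11.5). The last column is the share of simulated cohorts in which a t-test at 0.05 calls the deadlier group significantly shorter.

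| D (days) | Difference (days) | Significantly shorter |
|---|---|---|
| 3 | -1.4 | about 81% |
| 5 | -1.1 | about 59% |
| 7 | -0.8 | about 32% |
| 9 | -0.4 | about 11% |
| 11.5 | 0 | about 2% |
| 14 | +0.4 | about 1% |

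At D = 5, a rank test on the raw durations calls the deadlier group shorter in about 80% of cohorts. With mortality of 40% vs 30% and D = 5, the difference is 0.10 × (5 - 11.5) = -0.65 days, significant in about 25%.

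**Step 3: can a real difference be hidden?** Keep 45% vs 28% and D = 5, but let survivors of the deadlier phenotype stay 2 days longer (13.5 days).

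- Deadlier group: 0.55 × 13.5 + 0.45 × 5 = 9.68
- Other group: 0.72 × 11.5 + 0.28 × 5 = 9.68

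The difference is 0.0 days, so the longer stay in survivors disappears.

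**The case against.** **The direction is not fixed.** A reader might infer that the deadlier phenotype will always look better. The documents do not support that. The sign depends on whether decedents stay for less or more time than survivors, and the article gives no durations. The tables show the bias vanishing and then reversing. This stands, and the point is limited accordingly.

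**The phenotype contrast is uncertain.** Setting suppressed patients against all others is a simplification. The Discussion compares normal, suppressed and hyperdynamic states, puts higher mortality in both abnormal states, and also cites a study with better prognosis after a reversible fall in ejection fraction. The 45% vs 28% split is therefore only an illustration. The formula applies to any pair of groups with different mortality.

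**The statistical section names neither outcome, and an article condenses a fuller plan.** It is true that the link is inferred. But both outcomes are continuous, the stated rule for continuous variables is a comparison of means, and no other method is assigned to them. The objection is to what the stated rule does, not to a missing detail.

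**Free-days mostly re-detect mortality.** This stands too. Free-days favour the less lethal group even when survivors' stays are identical, so a clear free-days result is no evidence about duration.

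**The outcomes are secondary, and raw ICU days legitimately describe resource use.** Mortality will be reported beside them, so an alert reader could see the problem. This lowers the severity but does not make the difference in means interpretable as speed of recovery.

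**Conclusion.** The point holds in conditional form. Under the stated rule, a difference between phenotypes in mean ICU stay or ventilator days cannot be read as a difference in recovery, because it contains a term equal to the mortality gap times (decedent minus survivor stay). On the assumed inputs with 45% vs 28% mortality, that term runs from about -1.4 to +0.4 days as mean decedent stay goes from 3 to 14 days. With early deaths it is large enough to be declared significant often, or to cancel a true 2-day difference.

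The mortality range comes from literature that the article cites, not from this cohort. The day counts and the 45/28% split are assumptions. In-hospital and 28-day mortality and the prognostic models are untouched. It should be fixed as a cheap improvement to two secondary outcomes. It is not a flaw that undermines the study.

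**What to change.** State in the analysis section how deaths, and discharges counted as death, enter the two outcomes. Then use one or both of these:

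- Cumulative incidence of live ICU discharge and of live liberation from ventilation, with death (including discharge counted as death) as a competing event.
- ICU-free and ventilator-free days to day 28, with death scored 0, compared by a rank-based method.

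Report mortality and survivors-only durations beside them, as description. State how never-ventilated patients are handled.

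The cost is a few sentences. There are two downsides. Free-days mix mortality with duration, so their components must be shown. The dates of ICU discharge, extubation and death must be on the case report form. The article does not list them, so this needs to be checked and the dates added if they are absent.

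### Automatic discharge after a physician's judgement of irreversible disease appears to count as death, and the rule is not confined to in-hospital mortality, so 28-day mortality can be misclassified

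*Protocol article*

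**What the plan says.** All of this is in the protocol article, under Methods.

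- **Outcomes (Data acquisition).** "The primary outcomes are in-hospital and 28-day mortality rates".
- **Rule for some discharges (same paragraph).** "Severe and irreversible disease will be determined by the supervising physician", and, in the same sentence, the patient's "family chose automatic discharge due to local customary conditions indicating death". The wording is rough. It joins two conditions, a physician's judgement and a family's choice, and equates them with death. It does not say which mortality outcome the rule serves, and it gives no criteria for the judgement.
- **Follow-up (Data acquisition).** A closing visit is foreseen, but only in the missing-data text: "if an ending visit is missed, data from other points in time can be included in the analysis". It is not linked to vital status after discharge.
- **Safeguards on the exposure (Inclusion criteria).** "transthoracic echocardiograms will be performed by relevant qualified personnel and interpreted by two qualified personnel", and "In case of diagnostic disagreement, we will ask an expert panel for a resolution". The panel is described for echocardiographic disagreement only.
- **Use of the outcomes (Data statistical analysis).** "multifactor logistic regression and Cox survival analysis will be used to determine the factors of prognosis". Neither model is assigned to a particular outcome.

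**The concern.** Whether a patient is alive on day 28 is a fact that can be found out after discharge. A rule that settles it at the hospital door, from a physician's view of irreversibility and a family's decision, replaces that fact with a forecast. The forecast will often be right, but it will be wrong for some patients.

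The consequence depends on how those errors fall across phenotypes. If they are unrelated to phenotype, recorded mortality is too high and the phenotype contrast shrinks. If they are commoner in one phenotype, the study can report an association with mortality that is partly an association with a decision. The second route deserves attention here because the study exists to relate echocardiographic phenotype to mortality, and its Introduction and Discussion already describe suppressed and hyperdynamic hearts as carrying higher mortality. A physician who holds that view and has seen the scan might more readily call the disease irreversible.

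**Working it through.** No figure in the article depends on this rule, so there is nothing of the plan's own to reproduce. The check is a reading of the text followed by an illustration of size.

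**Reading**

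1. The mortality outcomes are named and the discharge rule follows in the same paragraph, with no restriction to in-hospital death. Applied as written, it also decides day-28 status.
2. The rule needs both conditions. A family-chosen discharge without the physician's judgement is not covered.
3. The exposure has two readers and an expert panel. No comparable step is stated for the judged part of the outcome.
4. The article does not say whether the supervising physician sees the echocardiogram. It states neither access nor masking.

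**Illustration A: miscoding in the suppressed group only, no true difference**

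Inputs from the article: mortality 33.5% (domestic figure, Discussion), prevalence 40% and N = 1,152 (Data acquisition), significance level 0.05, taken as two-sided. Group sizes: 0.40 × 1,152 ≈ 461 suppressed; 1,152 − 461 = 691 others. Assumption, not in the article: a share f of true survivors in the suppressed group is coded dead, and none in the other group.

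Apparent mortality, suppressed group: p1 = 0.335 + 0.665 × f. Other group: p0 = 0.335.

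Chance of p<0.05 (normal approximation) = Φ[(p1 − p0 − 1.96 × SE0) / SE1], with SE0 the pooled and SE1 the unpooled standard error.

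| f | p1 | p1 − p0 | Patients miscoded (461 × difference) | SE0 | SE1 | Odds ratio | Chance of p<0.05 |
|---|---|---|---|---|---|---|---|
| 2% | 34.8% | 0.0133 | about 6 | 0.0285 | 0.0285 | 1.06 | about 7% |
| 5% | 36.8% | 0.0333 | about 15 | 0.0287 | 0.0288 | 1.16 | about 21% |
| 10% | 40.2% | 0.0665 | about 31 | 0.0289 | 0.0290 | 1.33 | about 63% |

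For f = 5%: (0.03325 − 1.96 × 0.02865) / 0.02876 = −0.80, and Φ(−0.80) = 0.21. The formula counts only results in the direction of the miscoding; adding the opposite tail moves the first row from 6.8% to 7.6% and leaves the others practically unchanged. The nominal two-sided level is 5%. If 2% or 5% of survivors in the other group are also coded dead and the same excess applies, the odds ratios stay between 1.06 and 1.33.

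**Illustration B: miscoding unrelated to phenotype**

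Assume true mortality of 40% versus 30%. The odds ratio is (0.40/0.60) / (0.30/0.70) = 1.56. If a share f of survivors in both groups is coded dead, mortality becomes 0.40 + 0.60f and 0.30 + 0.70f:

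- f = 5%: 43.0% versus 33.5%, odds ratio 1.50
- f = 10%: 46.0% versus 37.0%, odds ratio 1.45
- f = 20%: 52.0% versus 44.0%, odds ratio 1.38

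There is no false association in this case, only dilution.

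**The case against.** The rule has a rationale. Patients sent home after a judgement of irreversible disease will often die soon, and coding them all as survivors would misclassify too, perhaps more. That stands. It argues for finding out what happened to them, not for reversing the rule.

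Several stronger readings are tempting, and the article does not support them:

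- **That the outcome is phenotype-aware.** The article never says that the physician sees or uses the phenotype when judging irreversibility, and a condensed article may leave masking to the full protocol. Influence is possible, not documented.
- **That vital status is never checked, or that the death date is wrong.** The first is an inference from silence, since a closing visit is mentioned. For the second, the article does not say which date is recorded.
- **That live discharge will be censored in a Cox model of in-hospital death.** Both logistic and Cox models are planned without being matched to outcomes. Logistic regression for in-hospital death and Cox for 28-day death is at least as natural a reading.
- **That the false-positive rate is about 41%.** The arithmetic works for a 5-point excess (38.5% versus 33.5%: SE 0.0289, 0.05/0.0289 = 1.73, P(Z > 1.96 − 1.73) = 0.41). But that excess has no source. It means about 23 false deaths (0.05 × 461), or 7.5% of that group's survivors (0.05/0.665), with none elsewhere.
- **That in-hospital mortality should cease to be primary.** In an observational cohort that is a preference and does not follow from this rule.

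**Conclusion.** The concern holds in limited form. As written, the rule appears to record as dead those patients who are both judged severe and irreversible and discharged by family choice, and it does so without being confined to in-hospital mortality. For the 28-day outcome this is a badly fixed definition rather than missing detail, because a verifiable status is replaced by a judgement.

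The size cannot be fixed from the article, which gives no share of such discharges and no survival after them. Under the assumed rates, miscoding confined to the suppressed group lifts the chance of a spurious p<0.05 from 5% to about 7%, 21% or 63%. Miscoding unrelated to phenotype leaves a diluted odds ratio (1.56 falling to between 1.50 and 1.38). Which applies depends on whether the phenotype influences the judgement, which the article leaves open. The point merits a change to the plan, but it is not evidence that the results will be biased.

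**What to change.** **28-day mortality**

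- State the discharge rule in one clear sentence and say which outcome it serves.
- Obtain vital status and date of death at day 28 for every patient discharged earlier, automatic discharges included.
- Count an automatic discharge as a death only when day-28 status cannot be obtained, and flag each such patient on the case report form.
- Report a sensitivity analysis with confirmed deaths only.

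**In-hospital mortality**

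- Flag the patients counted as deaths under the rule and report results with and without them.
- If this outcome is analysed by Cox regression, do not treat live discharge as non-informative censoring.

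**Cost.** Follow-up calls for early discharges, one flag on the form and one extra analysis. This concerns how the outcome is recorded and asks for no change in patient care.

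**Limit.** If knowledge of the phenotype led to earlier discharge and the patient then died, the death is real and a day-28 check would confirm it. The change removes misclassification; it does not remove any effect of the scan on decisions about care.
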